### Methods and planned analyses

#### Participants

All participants included in the total sample are invited to participate in a 1.5-hour MRI protocol. P2-specific exclusion criteria include the presence of MRI-incompatible metal implants, history of stroke, and claustrophobia. We anticipate approximately 50% of the entire sample (n=200) will be eligible and consent to MRI. Eligible participants are invited for a longitudinal scan at one-year follow-up; we anticipate 25% (n=50) being available and consenting to the repeat scan to assess longitudinal stability of our main measures. Given the specific safety requirements of MRI, it is possible that the final P2 sample will not be fully representative of the P1 sample in terms of demographics and clinical characteristics. If this is the case, we will consider this important caveat in interpreting any results using joint P1-P2 and conduct sensitivity analyses where appropriate.

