### Objectives

The primary objective of P3 is to investigate the impact of inflammasome activation on EF domains in SUDs. Its secondary objective is to investigate the impact of inflammasome activation on structural and functional brain parameters in SUDs (integration with P2).

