### Methods and planned analyses

#### Blood collection, sample preparation, and storage

P3 draws on the same participant pool recruited for P1. Blood is collected into two EDTA (8 cc) and one citrate (4.5 cc) tubes. After processing, the plasma and buffy coat aliquots are immediately stored at -80°C until analysis. Blood samples and extracted DNA are banked for potential future integrative analyses (see Project 7).

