#### Proposed analysis

To test the association of the biomarkers with the three EF domains and neuroimaging outcomes, we will use Pearson correlation and linear multiple regression models. The linear models can be expanded to include potential covariates, if necessary. The total sample size of 400 subjects will be sufficiently powered to detect small effect sizes of correlation coefficients of 0.11 (α=0.05, statistical power of 80%) to 0.14 (α=0.05, statistical power of 95%).

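### Project 3 overstates its power: with 400 people a correlation of 0.11 has about 60% power, not 80%, and 0.14 has about 80%, not 95%; its imaging analyses have only about 200 people

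*Protocol article*

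**What the plan says.** The power statement closes the Proposed analysis section of Project 3. It begins "The total sample size of 400 subjects will be sufficiently powered to detect small effect sizes" and gives two pairs: "correlation coefficients of 0.11 (α=0.05, statistical power of 80%) to 0.14 (α=0.05, statistical power of 95" per cent. Sidedness is not given.

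The paragraph opens with the analyses that this statement supports. For the association of the "biomarkers with the three EF domains and neuroimaging outcomes, we will use Pearson correlation and linear multiple regression models". So both the executive function (EF) outcomes and the imaging outcomes are in scope, and 400 is the only sample size named.

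Two other sections set the numbers available:

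- Project 3, Blood collection, sample preparation, and storage: "P3 draws on the same participant pool recruited for P1". The Project 1 recruitment target is 400.
- Project 2, Participants: "We anticipate approximately 50% of the entire sample (n=200) will be eligible and consent to MRI".

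Imaging is a stated aim of Project 3. Its Objectives section says: "Its secondary objective is to investigate the impact of inflammasome activation on structural and functional brain parameters in SUDs (integration with P2"). The second hypothesis there (H2, parts a to c) concerns grey matter, network activation and connectivity.

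**The concern.** Test, sample size, alpha, effect size and power are all stated, so the claim can be checked as it stands. A correlation of 0.11 is very small for 400 people to detect with 80% power, and 0.14 is close to what 400 people usually detect at 80%, not 95%.

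The sample size is a second problem. Imaging outcomes exist only for those who are scanned, about half the cohort, so a power figure based on 400 cannot describe them.

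The paragraph is Project 3's only sample-size justification and covers its primary objective. A reader who trusts it would expect to miss a true correlation of 0.11 once in five times. If the real miss rate is much higher, a null inflammasome result could be taken to exclude effects that the study was not powered to find.

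**Working it through.** **Inputs.** From Project 3, Proposed analysis: Pearson correlation, N = 400, alpha = 0.05, r = 0.11 with 80% power, r = 0.14 with 95% power. From Project 2, Participants: about 200 with MRI. Assumption: two-sided test, with one-sided shown as the alternative.

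**Formula.** By Fisher's z, power = Φ(atanh(r) × √(N − 3) − z), where z = 1.960 two-sided or 1.645 one-sided. The opposite tail is negligible. The detectable correlation is tanh((z + z_power) / √(N − 3)), with z_power = 0.842 for 80% and 1.645 for 95%. The sample size needed is ((z + z_power) / atanh(r))² + 3.

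**Check of the method on the programme's other correlation claim.** Project 2, Proposed analysis, says that n = 200 gives more than 0.80 power at r = 0.2. Here atanh(0.2) = 0.2027 and √197 = 14.036; their product is 2.846, and Φ(2.846 − 1.960) = 0.812. That claim reproduces.

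**Attempt to reproduce the Project 3 figures.** √397 = 19.925.

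- r = 0.11: atanh = 0.1104, product 2.201. Two-sided Φ(0.241) = 0.595. One-sided Φ(0.556) = 0.711. Stated: 0.80.
- r = 0.14: atanh = 0.1409, product 2.808. Two-sided Φ(0.848) = 0.802. One-sided Φ(1.163) = 0.878. Stated: 0.95.

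A noncentral t calculation gives 0.598 and 0.805 (two-sided). A simulation of the two-sided Pearson test with 40,000 replicates gives 0.595 and 0.802.

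**Other readings tried.**

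- *Rounding.* Even r = 0.115 and r = 0.145 give 63% and 83% two-sided, or 74% and 90% one-sided.
- *Regression F test with 2 to 5 predictors, the stated value taken as the multiple correlation.* Power falls to 35–49% and 55–71%.
- *Stated value taken as f².* Power is about 100% for both, which matches neither figure.
- *Two-sided alpha of 0.20.* Power is 82% and 94%. This comes close, but contradicts the stated 0.05.

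**What 400 people detect, and what the stated pairs need.**

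| | 80% power | 95% power |
|---|---|---|
| Stated r, N = 400 | 0.11 | 0.14 |
| Detectable r, N = 400, two-sided | 0.140 | 0.179 |
| Detectable r, N = 400, one-sided | 0.124 | 0.164 |
| N needed for stated r, two-sided | 647 | 658 |
| N needed for stated r, one-sided | 510 | 548 |

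**Imaging outcomes, n = 200, two-sided.**

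- Power at r = 0.11: Φ(0.1104 × 14.036 − 1.960) = Φ(−0.410) = 0.341.
- Power at r = 0.14: Φ(0.1409 × 14.036 − 1.960) = Φ(0.018) = 0.507.
- Detectable r at 80%: tanh(2.802 / 14.036) = 0.197.
- Detectable r at 95%: tanh(3.605 / 14.036) = 0.251.

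**Miss rates for a true r of 0.11, two-sided.** At N = 400, 1 − 0.595 = 0.405, about 2 in 5. At n = 200, 1 − 0.341 = 0.659, about 2 in 3. The stated power implies 1 in 5.

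**The case against.** The arithmetic has no defence, but several points bear on its size and weight.

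*Sidedness is not stated, and the Project 3 hypotheses are directional.* A one-sided reading is therefore possible. This stands as a range: 60–71% power for r = 0.11 and 80–88% for r = 0.14. The miss rate at r = 0.11 would be about 3 in 10 instead of 2 in 5. Both stated figures fail at either end.

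*The power sentence names 400 as its base and does not itself mention imaging.* The imaging outcomes appear in the opening sentence of the same paragraph. The expected MRI number is given openly in Project 2, with an 80% power figure at r = 0.2. This partly stands: the information is in the article. But Project 3 offers no other sample size for its own secondary objective, so a reader of that section is left with 400.

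*The 200 is an expectation.* True. It is the programme's own planning figure, and the imaging results above depend on it.

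*The error changes no design decision.* The target of 400 is programme-wide, Project 3 is observational, and nothing shows that the target came from this calculation. A detectable correlation of 0.14 is still small. All of this is fair and limits the consequence to interpretation. It does not make the stated power correct.

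*Sharing alpha across the three EF domains is not something the article prescribes.* Agreed. Such a rule may sit in the analysis plan, and the finding does not depend on it.

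**Conclusion.** The concern holds. At alpha 0.05, neither stated power is reached under any standard reading tried. Two-sided, the claims are too high by about 20 percentage points at r = 0.11 (80% against 59.5%) and about 15 at r = 0.14 (95% against 80.2%). One-sided, the shortfalls are about 9 and 7 points. The correlation that 400 people detect with 80% power is 0.14, which the article pairs with 95%.

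For the imaging objective the basis of 400 does not apply. With about 200 people, power is 34% and 51% at the two stated correlations.

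These figures assume complete blood and EF data on all 400, MRI on 200, and no adjustment for multiple testing. Missing samples or an adjustment would lower power further. The sample size itself is not shown to be inadequate; the statement about what it can detect is wrong.

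**What to change.** Replace the last sentence of Project 3, Proposed analysis, with wording such as: with 400 participants the study has 80% power to detect a correlation of 0.14 and 95% power to detect 0.18 (two-sided alpha 0.05); for imaging outcomes, with about 200 participants expected, the corresponding values are 0.20 and 0.25.

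If a one-sided test was intended, say so and give 0.12 and 0.16 for 400 participants, and 0.18 and 0.23 for 200.

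Only if the three EF domains in Project 3's first hypothesis are to share alpha (0.05/3 each), add that the 80% value at N = 400 becomes 0.16: z = 2.394, so tanh((2.394 + 0.842) / 19.925) = 0.161.

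The cost is one sentence and slightly less favourable detectable effects. Recruitment, tests and hypotheses do not change.

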## Project 4: to assess the role of repetitive transcranial magnetic stimulation (rTMS) on aberrant EF in the context of major depressive disorder in adult outpatients seeking treatment for AUD (NCT06299787)

### Background

Identifying specific neural and molecular mechanisms associated with EF deficits (P2 and P3) may guide future neuromodulatory and pharmacological treatments seeking to boost EF in adults with diverse SUDs and complex clinical presentations. To illustrate the potential utility of brain-based therapies targeting EF, Project 4 (P4) will conduct a clinical trial evaluating the efficacy of neuromodulation on EF in a complex subpopulation of CDiA participants presenting with AUD and Major Depressive Disorder (MDD).

Repetitive Transcranial Magnetic Stimulation (rTMS) of the PFC is FDA-approved for the treatment of MDD and a large body of evidence supports its safety and antidepressant efficacy (149–151). Many cognitive and psychological processes stemming from the PFC, are disrupted in both MDD and AUD (152), which are frequently comorbid (153, 154). Theta Burst Stimulation (TBS) is an efficient form of rTMS associated with both antidepressant effects (155) and alterations in plasticity in the cortex (156). Importantly, TBS takes about 1/6^th^ the time of standard rTMS, translating to a higher impact and consequently more efficient treatment at a population level.

Understanding the mechanisms underlying treatment response to rTMS is crucial to future therapeutic development. Previous studies have demonstrated that both rTMS and TBS target neurophysiological markers of GABA-receptor-mediated inhibition and this mechanism may be related to MDD treatment response (157–160). Although rTMS has shown promise for the treatment of SUDs (E.g (161), there have not been specific neurophysiological investigations into EFs and depressive symptomatology in the context of MDD comorbid with AUD. To address this gap, P4 will conduct a clinical trial evaluating the effects of bilateral TBS on EF in comorbid AUD and MDD. P4 will also investigate the correlation among rTMS treatment, indices of GABAergic inhibition and individual domains of EF (inhibition, updating, and set shifting). To further investigate therapeutic mechanisms, the P4 will incorporate an investigation of theta-gamma coupling (TGC), a neurophysiological index of PFC activity (172), during an N-back working memory task before and after rTMS treatment.

### Objectives

The primary objective of P4 is to conduct a double-blind randomized pilot study, consisting of two arms (bilateral TBS and sham) to investigate the effect of bilateral TBS on deficits in EF in the context of comorbid AUD and MDD. We will also measure alterations in TMS-EEG-indexed GABA receptor mediated inhibition and DLPFC TGC as potential mechanisms mediating therapeutic effects. We will also assess the direct associations between improvement in EF domains after bilateral TBS, with improvement in MDD symptoms.

P4 will test six interrelated hypotheses (H1-H6). Specifically, we hypothesize that, compared with sham TBS, 4 weeks of daily bilateral DLPFC TBS will lead to:

#### H1

Greater improvement in EF task performance;

#### H2

Greater proportion of individuals remaining abstinent from substance use;

#### H3

Greater amelioration of depressive symptoms (as indexed by decrease in HRSD-17 score) and suicidal ideation (as indexed by a decrease in Columbia-Suicide Severity Rating Scale score);

#### H4

Increase in GABA-receptor-mediated inhibition indices;

#### H5

Increase in TGC proportional to improvements in EF;

#### H6 (exploratory)

Improvement in all EF domains (inhibition, updating, and set shifting) in conjunction with improvement in MDD symptoms (ie. more amelioration of MDD symptoms will be associated with improved EF).

### Methods and planned analyses

A total of 40 participants will be recruited from the CDiA pooled sample within 6 to 12 weeks of the baseline assessment for P1. Participants will be randomized in a 1:1 ratio to one of two different rTMS arms. The first arm will include bilateral TBS, applied as cTBS over the right DLPFC followed by iTBS applied over the left DLPFC. The second arm will be sham TBS. All participants will be asked to participate in 4 weeks of treatment, 5 days/week (i.e. weekdays). TMS-EEG will occur at treatment initiation (week 0) and treatment end (week 4). Baseline and post-treatment clinical measures will be administered to characterize each AUD patient. TBS will be administered using the MagPro X100 stimulator equipped with a Cool-B70 coil and Qooler fluid-cooling device (MagVenture, Farum, Denmark) positioned under MRI guidance using the Brainsight neuronavigation system. With a sample size of 20 participants per group and assumed large effect sizes, we will have 80% of statistical power to detect a significant difference between the active treatment arm and sham at a significance level of 0.05.

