### Methods and planned analyses

#### Design and participants

The CDiA Program aims to recruit a total sample of 400 adults seeking treatment for AUD and/or SUD to participate in this observational, longitudinal study involving clinical and cognitive assessments at baseline and at a one-year follow-up period (see **Table 1** for a comprehensive list of clinical and cognitive assessments and the time points of each assessment). Inclusion criteria are: (1) 18 - 60 years of age; (2) meeting diagnostic criteria for a current (past year) AUD and/or SUD (not counting nicotine- or caffeine-related disorders); and (3) seeking support for substance use concerns. Exclusion criteria include: (1) acute intoxication or withdrawal; (2) active psychosis; (3) acute suicidality; and (4) history of severe head injury, dementia, severe neurodevelopmental disorders, and other medical conditions or medications that could severely impair cognition.

**Table 1 T1:** Schedule of clinical & cognitive assessments.

Procedure	Construct Measured	Baseline ^a^	Follow up ^b^	Year End ^c^
Informed Consent	N/A	✓		
Verbal confirmation of 12-hour abstinence and time of last substance use	Substance Use	✓		✓
Urinalysis and Breathalyzer	Substance Use	✓		✓
Performance-Based Measures				
CNS-Vitals ^¢ θ^	Cognitive Functioning: General	✓		✓
Iowa Gambling Task ^¢ θ^	Cognitive Functioning: Decision Making	✓		✓
Delay Discounting Task ^¢^	Cognitive Functioning: Decision Making	✓		✓
Probability Discounting Task ^¢^	Cognitive Functioning: Decision Making	✓		✓
Flanker Task ^¢ θ^	Executive Functioning: Inhibitory Control	✓		✓
N-back Task ^¢ θ^	Executive Functioning: Updating	✓		✓
Switch Task ^¢ θ^	Executive Functioning: Set Shifting	✓		✓
Interview-Based Measures				
Diagnostic Assessment Research Tool (55)^d^	AUD, SUD, and other mental health diagnoses	✓		✓
Timeline Follow Back (56)	Substance Use	✓		✓
Psychiatric Treatment History	Treatment History: Medications	✓		✓
Psychological Treatment	Treatment History: Psychological	✓		✓
Self-Report Measures				
Demographics ^$^	Identity	✓		
Bem Sex Role Inventory (Short Form) (68, 69) ^$^	Identity	✓		
Lifetime substance use history (70) ^$^	Substance Use	✓		
Alcohol Use Disorders Identification Test (71) ^$^	Substance Use and Harms	✓		✓
Drug Use Disorders Identification Test (72) ^$^	Substance Use and Harms	✓		✓
Fagerström Test for Nicotine Dependence (73) ^$^	Substance Use and Harms	✓		✓

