### Power analysis and data analytic plan

Multiple regression will be used with the clinical, functional, and demographic factors entered as simultaneous predictors of each EF domain to test hypotheses about which factors are most strongly associated with specific EF domains (H1a and H1b).

For H1c, we will conduct latent profile analyses using domains of EF as indicators of discrete latent profiles of relative deficits and biases. We will then examine the prediction of membership in these latent profiles from substance use profiles.

For H1d, latent growth curve modeling will be used to model changes in substance use frequency, SUD severity, and functional outcomes over the follow up time points. Next, rate of change will be examined as a function of baseline EF (H1a) by regressing variability in the slopes for the growth factors on baseline EF deficits and biases. These will be included as simultaneous predictors in the model to examine the specific EF domains and biases that are most predictive of change in the clinical and functional outcomes.

For H1e, we will use a generalized linear mixed effects modelling approach. EF deficits and biases will be modelled as dependent variables and time will be entered as a within-subjects factor to determine if there is significant within-person change from baseline to one year follow up. Changes over time in SUD symptoms and functional outcomes will be modelled using the same approach, with changes in EFs included in the models as a time-varying predictor of changes in these outcomes.

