### TBS treatment procedure

TBS will be delivered to the DLPFC bilaterally, with neuronavigation determined through structural MRI. The structural MRI utilized to derive the brain target will have been completed as part of P2. The coil position selection will start by identifying MNI152 stereotaxic coordinates (x, y, z) of (–38, +44, +26) and (26, 38, 44) in the left and right DLPFC, respectively, which we have shown to be effective targets for rTMS in alleviating symptoms of MDD (162). Bilateral TBS will be delivered as follows: R-DLPFC cTBS: 40s uninterrupted bursts (triplet 50 Hz bursts, repeated at 5 Hz, 40s on, 600 pulses total) followed immediately by L-DLPFC iTBS: (triplet 50 Hz bursts, repeated at 5 Hz, 2s on and 8s off, 600 pulses total). For intensity of stimulation we will use 120% RMT. Our work in over 200 people stimulating PFC suggests that 120% RMT is the maximum that should be used for negligible risk of seizure and other serious adverse effects beyond the expected scalp pain and headache during early treatment sessions (163, 164).

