### Clinical assessments

Participants will be initially screened with the MINI and C-SSRS. Interested and potentially eligible participants will complete a subsequent interview to address all criteria outlined above to confirm eligibility. The 17-item Hamilton Rating Scale for Depression (HRSD-17) (168) will be our tertiary clinical outcome measure. The tertiary clinical outcome criteria will be a decrease in HRSD-17 score at treatment end compared to baseline (150, 162). The HRSD-17 will be performed at baseline, weekly and at the end of the rTMS treatment course. The Columbia-Suicide Severity Rating Scale (C-SSRS) will be used to evaluate suicidality. This reliable and valid scale has been used in randomized clinical trials and is able to predict completed suicide (169). The C-SSRS has been reported as an effective measure for diagnosis and treatment across several diagnoses (170–172) with high internal consistency, and interrater reliability (172–176). The C-SSRS will be performed at baseline, weekly and at the end of the rTMS treatment course. TMS Adult Safety Screen (TASS) (166) will be used at recruitment and baseline to ensure that participants are safe to participate in rTMS treatment trials. To enhance integration with other projects, we will re-administer the EF cognitive assessments within one week prior to the start of rTMS and at the end of the 4-week course of rTMS.

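### The stated Project 1 change models and Project 2 follow-up analyses have no term or exclusion for the 40 cohort members who enter the Project 4 rTMS trial during follow-up

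*Protocol article*

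**What the plan says.** All references are to the protocol article.

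- **Cohort.** Project 1, Design and participants, describes an observational longitudinal study: "The CDiA Program aims to recruit a total sample of 400 adults seeking treatment for AUD and/or SUD". Table 1 schedules the EF tasks at baseline and year end only. Functional outcomes are also collected every two months.
- **Trial inside the cohort.** The methods section of Project 4 sets the source and timing of recruitment: "A total of 40 participants will be recruited from the CDiA pooled sample within 6 to 12 weeks of the baseline assessment for P1". On allocation it says: "Participants will be randomized in a 1:1 ratio to one of two different rTMS arms", one of them sham, with four weeks of treatment. The Project 4 objectives name EF deficits as the target.
- **Extra EF testing.** Project 4, Clinical assessments: "we will re-administer the EF cognitive assessments within one week prior to the start of rTMS and at the end of the 4-week course".
- **Overlap with imaging.** Project 4, TBS treatment procedure: "The structural MRI utilized to derive the brain target will have been completed as part of P2". Project 2, Participants, expects 200 baseline scans and 50 participants "consenting to the repeat scan to assess longitudinal stability of our main measures".
- **Models.** Project 1, Power analysis and data analytic plan, says for H1e that "time will be entered as a within-subjects factor to determine if there is significant within-person change from baseline to one year follow up", with EF change then used as a time-varying predictor of symptoms and function. H1d regresses growth slopes on baseline EF. Project 2, Proposed analysis, names age, sex and primary substance as covariates. The Limitations section adds recency of use for all analyses. None of these places mentions Project 4 participation or arm.

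**The concern.** The programme creates a randomised exposure, plus additional testing, inside the cohort whose course it wants to observe. Both fall between the two time points that H1e compares, and treatment can overlap the month-2 and month-4 assessments that feed the H1d slopes.

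Three results are exposed.

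- **Mean EF change (first part of H1e).** It can include a stimulation effect in 20 people and a retest gain in 40. Project 2 chose different in-scanner tasks to limit practice effects, so the authors regard practice on EF tasks as a real matter.
- **The link between EF change and clinical change (second part of H1e), and the H1d slopes.** Project 4 predicts that active stimulation improves EF, abstinence and depression together. If it does, it is an unmodelled common cause of the changes that H1e relates to one another.
- **Project 2 stability.** The sample is only about 50, so a handful of actively treated people can lower the estimate for reasons unrelated to the stability of the measure.

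**Working it through.** **1. The plan's own counts.** 400 × 0.50 = 200 baseline scans, and 200 × 0.25 = 50 repeat scans. Both reproduce.

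**2. Overlap.**

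| Sample | Project 4 members | Active |
|---|---|---|
| Project 1, 400 | 40 (10%) | 20 (5%) |
| Project 2 baseline, 200 | 40 (20%) | 20 (10%) |
| Repeat scans, 50, at 25% return | 40 × 0.25 = 10 (20%) | 5 (10%) |
| Repeat scans, 50, extreme: all return | 40 (80%) | 20 (40%) |

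**3. Timing and test count.** Entry at weeks 6 to 12 plus four weeks of treatment ends at about weeks 10 to 16, some 8 to 10 months before year end. Planned EF sessions are 2 + 2 = 4 for Project 4 members and 2 for the rest.

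**4. Shift in the H1e mean.** Let d be the active effect still present at month 12 and g the gain from the two extra sessions, both in SD units.

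Shift = (20/400)d + (40/400)g

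The documents give neither value; Project 4 says only that it assumes large effects. I take d from 0.3 to 0.91 (0.91 is what 20 per arm needs for 80% power in a two-sided 5% t-test) and g from 0 to 0.3.

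- d = 0.3, g = 0: 0.05 × 0.3 = 0.015 SD
- d = 0.91, g = 0: 0.05 × 0.91 = 0.046 SD
- d = 0.91, g = 0.3: 0.0455 + 0.030 = 0.076 SD

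**5. Effect on the H1e test.** Assume no change in anyone else, all 400 followed, and test-retest correlation ρ from 0.5 to 0.8 (assumed).

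Variance of change = 2(1 − ρ) + v, with v = 0.05(d + g)² + 0.05g² − shift²

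SE = √(variance/400), and rejection rate = Φ(shift/SE − 1.96) + Φ(−shift/SE − 1.96)

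- Low end (d = 0.3, g = 0, ρ = 0.5): variance 1.004, SE 0.050, ratio 0.30, rejection 6%.
- High end (d = 0.91, g = 0.3, ρ = 0.8): v = 0.0732 + 0.0045 − 0.0057 = 0.072, variance 0.472, SE 0.034, ratio 2.20, rejection 59%.
- d = 0.91 with no practice gain: 14% to 28% over ρ = 0.5 to 0.8.

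**6. Effect on stability.** Take a true value of 0.80, a share p actively treated and a shift d in their second scan. The added variance is v = p(1 − p)d², and the correlation becomes 0.80/√(1 + v).

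| Active of 50 | d = 0.5 | d = 0.91 |
|---|---|---|
| 5 (p = 0.1) | v = 0.0225, r = 0.79 | v = 0.0745, r = 0.77 |
| 20 (p = 0.4) | v = 0.060, r = 0.78 | v = 0.199, r = 0.73 |

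An absolute-agreement ICC also penalises the mean shift: 0.80/[1 + v/2 + (pd)²/2]. For p = 0.4 and d = 0.8 this is 0.80/(1 + 0.077 + 0.051) = 0.71. At d = 0.91 it is 0.80/(1 + 0.099 + 0.066) = 0.69, so the lower end is approximate. Applying such an effect to imaging measures is itself an assumption.

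**7. Cost of leaving the 40 out.** Detectable mean change (80% power, two-sided 5%) is 2.80/√N: 0.140 SD of change at N = 400 and 0.148 at N = 360.

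**The case against.** The strongest reply is that this is silence in a condensed article. Nowhere does it say that Project 4 members will be analysed like everyone else, and a full analysis plan may deal with them. That stands as a limit on the wording. It does not remove the point, because the article does state its models and covariates and discusses sample overlap only as a matter of representativeness. Followed as written, those models pool the trial participants.

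A second reply is that the cohort is meant to be naturalistic: the Discussion expects varied treatments, and H1d is framed as going beyond treatment engagement and healthcare utilization. This stands in part. Real improvement in a treated member is not in itself an error for H1e. However, extra testing is a measurement artefact rather than recovery. The analytic plan does not list the H1d adjustment terms, and the Table 1 treatment-history items cover medications and psychological treatment. Participants blinded to arm could not report it anyway.

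A reader might also infer stronger things that the documents do not support:

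- **That all 40 receive the intervention.** Allocation is 1:1 with sham, so 20 do.
- **That contamination is demonstrated.** The larger figures need a large effect undiminished 8 to 10 months after treatment, a lasting practice gain and no change in the other 360. The low end is close to the nominal 5%.
- **That H1b is affected.** Its stated test is a regression with no change component.
- **That Project 7 overlooks the trial.** Its objectives and Table 4 include Project 4 outcomes.

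**Conclusion.** The point holds as a possible bias that the stated analyses leave uncontrolled. The overlap, the timing, the doubled EF testing and the absence of any Project 4 term or exclusion all follow from the text.

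For Project 1 the likely effect is modest: a mean shift of about 0.015 to 0.08 SD, with a 5% test rejecting about 6% to 59% of the time if there is no other change. For Project 2, a stability of 0.80 would read about 0.77 to 0.79 if Project 4 members return at the anticipated rate. It would read about 0.71 to 0.78 only if all 20 actively treated people are rescanned. These ranges rest on assumed effect size, persistence, practice gain and retest correlation, and on full follow-up; the documents give none of the first four. The correction is worth making because it costs little and protects the main longitudinal claims.

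**What to change.** - **H1d, H1e and H2b.** Once Project 4 is unblinded, add Project 4 status (none, sham, active) and its interaction with time. In the H1d growth model, this means regressing intercept and slope on status. At minimum, report a sensitivity analysis without Project 4 participants.
- **Project 2 stability.** Estimate it without participants who received active stimulation.
- **No separate covariate for the number of EF sessions.** As planned it is 4 for every Project 4 member and 2 for everyone else, so it is collinear with status apart from missed sessions.

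**Cost.** This is analysis wording only, since allocation is recorded in Project 4. A three-level factor with its time interaction adds up to four parameters per model (two main effects, two interactions). The sensitivity analysis uses 360 rather than 400. The stability sample falls from 50 to about 45 at the anticipated return rate (50 − 5), or to 30 in the extreme case (50 − 20). The arm-specific analyses must wait for unblinding; the analysis excluding all Project 4 members need not.
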